### Sample size

With 80 subjects this study would have a 90% power to show an absolute reduction in risk of 1% based on a standard deviation in the change of risk of 2.7% with a two sided p-value of 0.05. To account for potential subject drop out and loss to follow-up of 20% we will aim to recruit 100 subjects.

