### Statistical analysis

Univariate comparisons between groups will be conducted using chi-square test for equal proportion (or Fisher's exact tests where numbers are small) and reported as numbers and percentages. Continuous normally distributed variables will be compared using Student's t-tests and reported as means (standard error) whilst non-parametric data will be compared using Wilcoxon rank-sum tests and reported as medians (interquartile range). Pairwise differences between pre and post values will be calculated using paired t-tests for normally distributed data and Wilcoxon sign rank tests for non-normally distributed data. To account for the large number of comparisons being made, we will employ a reduced 2-sided p-value of 0.01 to indicate clear statistical significance.

If any parameter from POC finger prick testing is found to be outside the measurable range for the machine, the value of the closest measurable limit will be given to that patient.

Health behaviours will largely be measured using existing scales associated with the survey instruments incorporated into baseline and follow-up assessment. For the dietary assessment, no validated tools are available for use in an Australian population so a study-specific tool has been devised. This tool is a 13-item questionnaire addressing dietary quality in this study population and using previously validated questions from the National Nutrition Survey and Cancer Council of Victoria Food Frequency Questionnaire relating to the nutrients of concern for primary prevention of CVD [27,28]. Responses for each item will be scored between zero (least healthy response option) and 10 (healthiest option) - consistent with the developing literature in this area of nutrition research [33]. This scoring allows for an overall diet score to be generated ranging from 0 to 130.

The general quality of dietary intake will be interpreted using the guidance provided in table 1.

**Table 1 T1:** Scoring mechanism used to assess overall quality of dietary intake

Diet score using nutrition tool	Interpretation
104-130	High level of compliance with CVD dietary guidelines (80% or more)

78-103	Medium level of compliance with CVD dietary guidelines (60-79%)

77 or less	Low level of compliance with CVD dietary guidelines (59% or less)

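### The stated 90% power assumes a two-sided 0.05 test, but the only significance threshold in the analysis section is 0.01, at which power for the primary outcome is about 75%

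*Protocol article*

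**What the plan says.** The Primary outcomes section of the protocol article names one primary outcome: the mean change in estimated 5-year risk of CVD onset. The Outcomes examined section sets the interval as baseline to six months.

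The Sample size section powers the study on that outcome. It states "this study would have a 90% power to show an absolute reduction in risk of 1" per cent, based on "a standard deviation in the change of risk of 2.7" per cent and "with a two sided p-value of 0.05". The basis is 80 patients, raised to 100 recruited to allow for 20% loss.

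The Statistical analysis section, which follows directly, assigns paired t-tests (or signed-rank tests for non-normal data) to pre/post differences. These are the only tests in the article that fit the primary outcome. The next sentence gives the significance rule: "To account for the large number of comparisons being made", the authors write, "we will employ a reduced 2-sided p-value of 0.01 to indicate clear statistical significance". No other threshold appears in that section, and the primary outcome is not set apart.

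**The concern.** The two sections fix different significance levels for what appears to be the same test. The power claim describes the chance of reaching p < 0.05. The analysis rule says a result is clearly significant when it reaches 0.01. A reader who takes the 90% at face value will think the study more likely to meet its own criterion than it is.

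The reason given for 0.01 also fits the primary outcome poorly. A stricter threshold guards against chance findings across many tests. A single pre-specified primary outcome does not need that protection merely because a list of secondary outcomes is tested beside it.

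The interpretation of the main result is at stake. If the primary p-value falls between 0.01 and 0.05, the sample size section supports calling the result positive and the analysis section does not. The choice between them could then be made after the data are seen.

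**Working it through.** **Inputs, all from the protocol article**

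- Evaluable patients: n = 80 (Sample size)
- Mean within-patient reduction: δ = 1 percentage point (Sample size)
- SD of the change: σ = 2.7 percentage points (Sample size)
- Two-sided α: 0.05 in Sample size, 0.01 in Statistical analysis
- Test: paired t-test on a single cohort (Study design and setting; Statistical analysis)

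**Method**

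For a paired t-test, power = P(|T| > t₁₋α/₂,ₙ₋₁), where T is noncentral t with n − 1 degrees of freedom and noncentrality λ = (δ/σ)√n.

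Here δ/σ = 1/2.7 = 0.370, so λ = 0.370 × √80 = 3.31 on 79 degrees of freedom.

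**Step 1: reproduce the stated figure (α = 0.05)**

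- Critical value 1.990; power = 90.5%.
- Normal approximation: Φ(3.31 − 1.96) = 91.2%.
- Smallest n for 90%: 79 (normal approximation 77).
- Allowance for loss: 80/(1 − 0.20) = 100.

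The sample size section is therefore correct on its own terms, and the test behind it is a paired test at two-sided 0.05.

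**Step 2: change only α to 0.01**

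- Critical value 2.640; power = 74.8%.
- Normal approximation: Φ(3.31 − 2.576) = 76.9%.

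Power falls by 90.5 − 74.8 = 15.7 points. The chance of missing the assumed effect goes from 9.5% to 25.2%.

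**Step 3: what 90% power at 0.01 would take**

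| Quantity | α = 0.05 | α = 0.01 |
|---|---|---|
| Power, 80 evaluable | 90.5% | 74.8% |
| Power if all 100 recruited are evaluable | 95.6% | 85.7% |
| Evaluable patients for 90% power | 79 | 112 |
| Recruited, at 20% loss | 99 | 140 |
| Reduction detectable with 90% power, n = 80 | 0.99 points | 1.19 points |

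**Step 4: the zone where the two sections disagree**

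The standard error of the mean change is 2.7/√80 = 0.302 points. The smallest observed reduction that is significant is then:

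- at 0.05: 1.990 × 0.302 = 0.60 points
- at 0.01: 2.640 × 0.302 = 0.80 points

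An observed mean reduction between about 0.60 and 0.80 points meets the rule in one section and fails the rule in the other. If the true reduction is 1 point, p lands between 0.01 and 0.05 about 16% of the time (90.5% − 74.8%).

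**The case against.** The best defence is that the 0.01 rule was never meant to displace 0.05 for the primary outcome.

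- **Graded evidence.** The section speaks of clear significance, which can be read as a label for stronger evidence, with 0.05 as the conventional level being reduced from. The two sections would then be compatible.
- **Secondary outcomes only.** The stated reason is the number of comparisons. That describes the long secondary list, not one primary outcome.
- **Low stakes.** This is a pilot whose first goal is feasibility. The Limitations section already says a larger controlled study is needed to determine effectiveness. A stricter threshold biases no estimate and raises no false-positive risk.
- **The loss is conditional.** The 75% assumes 80 evaluable patients; more could complete.
- **Condensed article.** Allocation of significance levels to endpoints is often left to a fuller document.

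Some of this stands. Both alternative readings are possible, the sample size arithmetic contains no error, and the harm is to the stated power and the clarity of the decision rule, not to the estimate.

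It does not remove the point. Neither reading is written down, and the 0.01 sentence directly follows the tests that apply to the primary outcome. Eighty evaluable patients is the protocol's own basis for its 90%, and even full retention of 100 gives only 85.7% at 0.01. Nor is anything here deferred to another document: the article states both thresholds, and they conflict. Pilot status does not excuse the mismatch either, because the authors chose to justify the sample size by a powered hypothesis test.

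**Conclusion.** The concern holds. Read as written, the significance rule gives the study about 75% power for its primary outcome with 80 evaluable patients, not the 90% stated. The fault is an inconsistency between two sections; the 90% is right for the 0.05 test it names.

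The 75% rests on the protocol's own effect (1 point), SD (2.7 points) and evaluable number (80), with a paired t-test and 0.01 applied to the primary outcome. If the authors intended 0.01 for other comparisons only, the 90% stands and what is missing is the sentence saying so. The calculation ignores clustering of patients within pharmacies and any loss of efficiency if the signed-rank test is used.

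**What to change.** State in the Statistical analysis section that the single primary outcome, mean change in estimated 5-year CVD risk, is tested at two-sided 0.05, and that 0.01 applies to the secondary and other comparisons. This matches the sample size section and the reason given for the stricter level. It costs one sentence.

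If 0.01 is intended for the primary outcome as well, correct the Sample size section: about 75% power for a 1-point reduction with 80 evaluable patients, or equivalently 90% power for a 1.19-point reduction. This costs a less favourable power statement.

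Neither option needs more patients. Only insisting on both 0.01 and 90% power for a 1-point reduction would, at 112 evaluable or 140 recruited (112/0.80). Whichever is chosen should be recorded before the six-month outcome data are analysed.

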## Discussion

The protocol and methods outlined above provide an intervention framework for managing multiple CVD risk factors in community pharmacy or other primary care settings. There is considerable incentive to demonstrate feasibility and effectiveness of such a service in community pharmacy, given the caution with which expanded roles for pharmacists in vascular care have been greeted by some [34]. While there is evidence of pharmacists' ability to conduct cardiovascular risk assessments and deliver basic post-screening counselling with some clinical benefits [35-37], evidence is lacking to demonstrate the full potential of their comprehensive, ongoing management of multiple CVD risk factors. This has led to concerns about fragmentation of care and lack of communication of results with doctors [34].

The HAPA model underpinning the approach to behavioural change was chosen because of its success in lifestyle-oriented diabetes prevention programs addressing similar risk factors for non-diabetic populations, including an implementation study based in Australian primary care [38,39]. Collection of process audit data is important to see how well this approach is adhered to by pharmacists. The emphasis on use of assessment scales for medicines adherence and various health behaviours is designed to promote ease of interpretation of clinical assessments by community pharmacists who are generalists in terms of their practice.

Several aspects of the protocol are context-specific and their adoption by other researchers or health service program managers may require consideration. Key issues include:

• The restriction of eligibility to patients aged 50-74 years is in keeping with national guidelines advocating that screening of overall risk outside the 45-74 years age bracket is not economically viable [9]

• The use of accredited pharmacists has been adopted to integrate with existing pharmacy skills networks and remuneration systems, and to alleviate time pressure for participating community pharmacists; there may be alternative workforce options to produce clinical reports in different settings.

• Patients with established diabetes and CVD will be excluded because there are existing evidence-based models of care already in practice or at implementation stage; and

• Community pharmacy represents a key setting and pharmacists are one of the most accessible healthcare providers in Australia, with expected competencies in both medicines use and health promotion.

### Limitations of study protocol

If the pilot testing indicates the feasibility of effective community pharmacy interventions, it will be important to validate this study with larger numbers and a control group to comprehensively determine effectiveness, cost-effectiveness and generalisability. Similarly, the six month timeframe limits the ability to test the sustainability of patient behaviour changes following the intervention, and self-report - while often the only option - for some health behaviours may be unreliable.

Validated dietary quality tools for cardiovascular health are not available for the Australian population, so we rely on a pilot with only face and content validity developed by one of the authors ([name]). Current Australian guidelines for lipid disorders claim a lack of evidence regarding appropriate cholesterol targets for primary CVD prevention, thus restricting guidance for practitioners. We relied on expert consensus developed from examination of eligibility criteria for subsidised lipid lowering medicines in Australia, previous guidelines, and values used for pathology lab reporting.

## Conclusions

The proposed intervention integrates guideline evidence and validated assessment tools where possible, but several key knowledge gaps remain to preventing an entirely evidence-informed approach. Protocols adopted for other primary CVD prevention studies have not been widely disseminated; hence this paper provides a starting point for future research and implementation programs in a primary care setting.
